### Randomisation

For Stage I, cluster randomisation (at the school level) will be employed for administrative convenience, to avoid control condition contamination, and for the ecological validity of providing the intervention at the cluster level. Schools will be randomised after they are recruited into the trial. The trial statistician who is not involved in the day-to-day running of the trial will perform the randomisation, and the identity of the school will be concealed from the statistician.

Schools will be randomised with a 1:1 allocation, as per a computer-generated randomisation schedule. Balance between the trial arms will be achieved by stratifying based on school size, school location (metropolitan vs. regional), school type (co-educational or gender selective) and Index of Community Socio-Educational Advantage (ICSEA) level. For Stage II, individual-level randomisation with a 1:1 allocation using a computer-generated randomisation schedule stratified by gender and depression severity scores will be employed. This procedure is automated through the Black Dog Institute research platform. Permuted block randomisation will be used at both stages but will not be disclosed to ensure concealment. Allocation to arms is not directly communicated to schools. However, because the study has no control intervention, schools, participants and study operational staff will be aware of school allocation to the intervention arm. With the exception of the trial data manager, other individuals not involved in the day-to-day running of the trial will remain blind to allocation. All outcome assessments are conducted electronically and not subject to assessor bias. Unblinding at the conclusion of analysis will be performed by the trial data manager with authorisation from the Trial Steering Committee.

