**Fig. 1 Fig1:**
[figure not shown]
Study flow

School principals will be contacted in the first instance. They will be given brief information sheets containing trial details. Schools will have the opportunity to hear more information over the telephone or via video conference. Those who wish to take part will be instructed to sign and return a letter of support. Upon receipt of the letter, schools will be accepted into the trial. In some instances, schools may approach the Black Dog Institute by submitting an expression of interest via a link on the study website (www.futureproofing.org.au) or by directly contacting staff at the Black Dog Institute.

After schools have consented, parents and students will be informed about the trial by their school via email or newsletter, depending on school preferences. A study invitation will be circulated to parents. This will include a link to an electronic information sheet and consent form. Here, parents and students can read information about the study, download a PDF copy of the study information sheet and provide electronic consent. Fourteen days following consent form distribution, schools with capacity will make follow-up telephone calls to parents who have not submitted a response. The option to provide verbal consent will be given to these parents. Students whose parents have consented to their participation will be given the opportunity to provide consent electronically at the start of the first study session. On the consent form, participants indicate whether they consent to different components of the study, including the sensor data collection and the linkage component, and whether they provide permission for their data to be included in a data repository for use by other researchers. Consent forms are available from the study website (www.futureproofing.org.au). No biological specimens will be collected. Students who do not provide active consent cannot participate in the trial. If a participant withdraws from the study, they are asked to indicate whether they give permission for their already provided data to be used by the study team. All recruitment strategies have ethical approval.

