### Procedure and participant timeline

Figure 1 shows the participant timeline and flow. An initial preparatory phase and first school visit will solicit parental and student consent, ensure that electronic study questionnaires are accessible by consented students and ensure that the appropriate study apps are installed on each student’s device. Each subsequent school visit will coincide with an assessment occasion. During these visits, students will access study questionnaires via a secure online portal, accessible using their mobile number and a one-time password sent via SMS. Study personnel will attend these school visits to assist with technical issues and participants’ questions. Following completion of baseline questionnaires, participants in the intervention condition will be instructed to commence the intervention both during class time and in their own time, and will receive notifications and reminders over the following 6 weeks to do so. Schools are required to schedule four 20-min in-class sessions for intervention completion but may choose to hold additional sessions (up to seven). Participants in the control condition will also be provided with equivalent class time to complete activities on the Future Proofing app. Students who do not complete assessments in school will also have the option to do this in their own time. Students will have up to 4 weeks following the scheduled assessment date to complete questionnaires at each time point, after which the assessment surveys will be locked and no longer accessible. During this 4-week window, automated electronic reminders will be sent to students to prompt completion, if required.

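### No stated step holds back a school's Stage I allocation until its students have consented and completed baseline, so consent and baseline PHQ-A can differ by arm

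*Protocol article*

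**What the plan says.** **School entry and randomisation.** Recruitment section: "Upon receipt of the letter, schools will be accepted into the trial", the letter being the principal's letter of support. Randomisation section: "Schools will be randomised after they are recruited into the trial". No later time point is given.

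**Approach to families.** Recruitment section: "After schools have consented, parents and students will be informed about the trial by their school via email or newsletter". Fourteen days after the forms go out, "schools with capacity will make follow-up telephone calls to parents who have not submitted a response". Students whose parents agreed "will be given the opportunity to provide consent electronically at the start of the first study session".

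**First visit.** Procedure and participant timeline: "An initial preparatory phase and first school visit will solicit parental and student consent". The same step covers access to the questionnaires and installation of the study apps on students' devices. Intervention students are told to begin SPARX once baseline is complete.

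**Who knows the arm.** The Randomisation section first says that schools are not told their allocation directly. It then accepts that, as there is no control intervention, "schools, participants and study operational staff will be aware of school allocation to the intervention arm". It gives no date for this awareness.

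**Analysis.** The primary contrast is change in self-reported PHQ-A from baseline to 12 months, with baseline differences controlled only where judged appropriate.

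**The concern.** In a cluster trial, randomising schools protects the comparison of schools. It does not protect the comparison of students if they are enrolled by people who already know the arm. Here the school informs the parents and may telephone those who have not replied, and one arm offers a programme while the other offers none. Knowledge of the arm could change how hard consent is pursued, which families agree, and how students answer a self-report scale at baseline.

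The stated safeguards address other risks. Hiding school identity from the statistician and keeping the permuted-block details undisclosed protect the allocation of schools. Electronic assessment removes assessor bias but not reporting by aware students. Intention-to-treat analysis cannot recover students who never consented. Bias of this kind does not shrink with sample size, whereas the standard error does.

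**Working it through.** **1. Order of events as written**

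| Step | Where | Timing given |
|---|---|---|
| School accepted | Recruitment | on receipt of letter |
| School randomised | Randomisation | after recruitment |
| Parents and students informed | Recruitment | after school consent |
| Parents telephoned | Recruitment | 14 days after forms go out |
| Student consent | Recruitment | start of first study session |
| Apps installed | Procedure | preparatory phase and first visit |
| SPARX started | Procedure | after baseline |
| Arm becomes known | Randomisation | undated |

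Nothing prevents the second and last rows from preceding consent and baseline.

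**2. The plan's own figures (Sample size section)**

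Design effect = 1 + (50 − 1) × 0.03 = 2.47. With r = 0.5 the SD of change is √(2 × (1 − 0.5)) = 1. A two-sample t-test at d = 0.3, two-sided α = 0.05 and power 0.80 needs 176 per arm; 176 × 2.47 = 434.7, so 435 per arm and 870 in total. With 30% attrition, 435/0.7 = 621.4, so 622 per arm and 1,244 in total. The plan's figures reproduce, and the order of consent and randomisation does not affect them.

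With 7,000 analysed, SE = √(4 × 2.47/7000) = 0.0376. The detectable effect is (1.960 + 0.842) × 0.0376 = 0.105 SD.

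**3. Size of a possible bias**

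Assumptions, none of them in the documents: no true effect; in one arm the odds of consent change by a factor of 1.22 per SD (log-odds 0.2); in the other arm consent is unrelated to symptoms; consent rate p of 20%, 50% or 80%. The shift in mean of the selected variable is about 0.2 × (1 − p) SD.

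*Consent depends on current symptoms.* With r = 0.5, half of the baseline difference remains at 12 months, so the change contrast is off by half of it and a baseline-adjusted contrast by 0.

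*Consent depends on stable symptom level.* The stable part has variance 0.5 on the scale of the score, so the baseline difference is 0.2 × (1 − p) × √0.5. It persists in full to 12 months, so the change contrast is off by 0. A baseline-adjusted contrast removes only half and is off by the rest.

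| Consent rate | Current symptoms: baseline difference | change bias | Stable level: baseline difference | adjusted bias |
|---|---|---|---|---|
| 20% | 0.16 | 0.08 | 0.11 | 0.06 |
| 50% | 0.10 | 0.05 | 0.07 | 0.035 |
| 80% | 0.04 | 0.02 | 0.03 | 0.01 |

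Numerical integration of the logistic model agrees with these values to the figures shown.

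*Baseline reporting only.* If awareness shifts baseline answers by δ in one arm and nothing else changes, the change contrast is off by δ and a baseline-adjusted contrast by 0.5δ.

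**4. Against the plan's targets**

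A bias of 0.05 SD is 0.05/0.3 = 17% of the Stage I target and 0.05/0.105 = 48% of the effect detectable with 7,000. With no true effect and a bias of 0.05 SD, the two-sided rejection rate is about 7.6% at 870 analysed (SE 0.107) and about 27% at 7,000 (SE 0.0376).

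**The case against.** **The order is inferred.** Randomisation is placed after school recruitment with no interval stated, the flow figure is not shown, and the article condenses a fuller protocol. This stands. A reader might infer that schools are definitely randomised and told their arm before any student consents; the article does not say so.

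**Schools are not told directly, and awareness is undated.** Awareness is explained by the absence of a control intervention, which could mean that schools notice it only when SPARX does or does not arrive. This is fair and weakens the point, but the article then accepts awareness without limiting it to the period after baseline.

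**App installation proves little.** A reader might infer from installation at the first visit that the arm must be known by then. The article does not say which apps are installed at that point, and both arms use the Future Proofing app, so this is only suggestive.

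**Consent materials look the same in both arms.** The information sheet, form and parent video are not described as arm-specific, and no difference in consent effort is documented. This lowers the likely size of the bias but does not rule it out.

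**The sizes are assumed, and half the cases show none.** Correct: the change contrast is unbiased under selection on stable level, and the adjusted contrast is unbiased under selection on current symptoms. A reader might also infer that the bias always amounts to a third to a half of the effect the trial is sized for. It does not: Stage I is sized for 0.3 SD, and 0.105 SD is derived here for the 10,000 scenario, which the article considered in order to supply Stage II.

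**Conclusion.** The concern holds as a design risk that the stated safeguards do not cover. As written, allocation appears able to be known before student consent and baseline, so who consents and what they report at baseline can differ by arm. The documents do not show that such a difference will occur, or in which direction; it could mimic a benefit or hide one.

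Under the stated assumptions the planned change contrast is biased by 0.02 to 0.08 SD if consent follows current symptoms and by about 0 if it follows stable level. In the latter case a baseline-adjusted contrast is off by about 0.01 to 0.06 SD. Neither analysis is therefore safe under both mechanisms. Such a bias is modest against the 0.3 SD target but material if the full sample is recruited and small effects are interpreted. Confidence is medium, because the order is inferred and the selection strength and consent rates are assumed.

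**What to change.** For all remaining schools and waves (about 188 of the 200 schools were planned for Waves 2 and 3), state the order explicitly and change it as follows:

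1. Generate or release each school's allocation only after its consent list is closed and its baseline questionnaires are submitted.
2. Before that point, install only the Future Proofing app, which both arms use; enable SPARX after baseline.
3. Book class sessions without knowledge of the arm. This is possible because control schools get equivalent class time.

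**Cost.** Schools learn their arm later. The SPARX installation moves from the first visit to after baseline, done remotely or in the first class session, which needs some scheduling and technical support. The sample size does not change, and SPARX is already meant to start only after baseline.

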### Participant risk management protocol

An independent Data and Safety Monitoring Committee (DSMC) has been established to monitor the quality of trial data and the safety of research participants. The DSMC will be responsible for safeguarding the interests of participants through regular monitoring, including participant safety and adverse events. This group will be responsible for monitoring the efficacy of the interventions being tested on primary outcomes, as well as the overall conduct of the study, including recruitment, protocol compliance, accuracy and completeness of data collection. This group will also provide recommendations with respect to continuing, modifying or terminating the trial, on the basis of feasibility or safety concerns, and will have access to unblinded data. This group can recommend the trial team be unblinded if there are serious safety concerns and meets every 6 months to review trial conduct. There is no anticipated harm from this trial, as it involves a population-based sample and evidence-based interventions. However, should there be any unanticipated harms, this will be monitored by the DSMC, who will provide recommendations about care for affected participants.

All students involved in the trial will be assessed for suicidal thinking and behaviour at each assessment point, using the SIDAS and the YRBS. If participants indicate serious suicidal thinking, plans or behaviour on study surveys, an alert will be triggered whereby the research team and school counsellor are notified immediately using a purpose-built study portal. School counsellors will then follow-up with students within 48 h to offer immediate support, or refer on when necessary, which is recorded in the portal. The research team will monitor this portal and directly contact any counsellors who have not indicated follow-up with students. If students have changed or left schools, parents will be notified. At the 48-month assessment point, when students are in their final year of school, they will also be asked about history of sexual abuse. If students indicate an experience of sexual abuse, this same process of notifying the school counsellor will be followed, and schools will assume the duty of care for mandatory reporting requirements. This information will be communicated to relevant university and school ethics committees, as well as the DSMC following each assessment point.

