**Methods:**

A randomised controlled trial targeting up to 10,000 Year 8 Australian secondary school students will be conducted. In Stage I, schools will be randomised at the cluster level either to receive the CBT intervention app (SPARX) or to a non-active control group comparator. The primary outcome will be symptoms of depression, and secondary outcomes include psychological distress, anxiety and insomnia. At the 12-month follow-up, participants in the intervention arm with elevated depressive symptoms will participate in an individual-level randomised controlled trial (Stage II) and be randomised to receive a second CBT app which targets sleep difficulties (Sleep Ninja) or a control condition. Assessments will occur post intervention (both trial stages) and at 6, 12, 24, 36, 48 and 60 months post baseline. Primary analyses will use an intention-to-treat approach and compare changes in symptoms from baseline to follow-up relative to the control group using mixed-effect models.

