### Aims

This trial will investigate the impact of two mental health apps on adolescent depression. The first objective of this trial is to determine whether delivering a CBT programme via smartphone application can prevent high school students in Year 8 from developing depressive symptoms compared to students in the control arm. This study will assess the effect of the programme on a range of secondary outcomes, which include mental health symptoms (distress, anxiety, insomnia) at post intervention, 6, 12, 24, 36, 48 and 60 months. The effect of a second intervention on depression in those who show elevated depressive symptoms 1 year after using the first SPARX app will also be evaluated. Individual differences associated with response to the interventions will also be investigated, including demographics, history of mental illness, personality factors, social support, social media use and gender identification, among a range of other variables (see Table 1). In the control group, these factors will be examined as possible predictors for the development of depressive symptoms and other mental health problems.

**Table 1 Tab1:** Summary of primary, secondary and tertiary outcome measures, potential mediating and risk factors, and data collection time points

Outcome measure		Baseline	Post (Stage I)	6 months	12months	Post (Stage II)^a^	24 months	36 months	48 months	60 months
Primary outcome measure										
Depression	Patient Health Questionnaire: Adolescent Version (PHQ-A)	✓	✓	✓	✓	✓	✓	✓	✓	✓
Secondary outcome measures										
Psychological distress	Distress Questionnaire 5 (DQ5)	✓	✓	–	✓	–	✓	✓	✓	✓
Anxiety	Spence Children’s Anxiety Scale (SCAS) including Generalized Anxiety and Social Phobia subscales	✓	✓	–	✓	✓	✓	✓	✓	✓
Insomnia	Insomnia Severity Index (ISI)	✓	✓	–	✓	✓	✓	✓	✓	✓
Tertiary outcome measures, potential mediating variable risk factors										
Suicidal ideation	Suicidal Ideation Attributes Scale (SIDAS)	✓	✓	–	✓	–	✓	✓	✓	✓
Suicide behaviour	Youth Risk Behaviour Survey (YRBS)	✓	✓	–	✓	–	✓	✓	✓	✓
Externalising behaviours	Strength and Difficulties Questionnaire (SDQ)	✓	✓	–	✓	–	✓	✓	✓	✓
Eating disorders	Screen for Disordered Eating (SDE)	✓	✓	–	✓	–	✓	✓	✓	✓
Self-harm	Single question from Self-Harm Questionnaire	✓	✓	–	✓	–	✓	✓	✓	✓
Alcohol use	Questions from previous National Drug and Alcohol Research Centre, UNSW studies	✓	✓	–	✓	–	✓	✓	✓	✓

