## Methods

### Trial design

This study is a randomised controlled, single-blind trial with two intervention stages, each consisting of two parallel arms (intervention and inactive control) with 1:1 allocation at each stage. Cluster randomisation will occur at the school level for the first intervention stage, stratified by school size, school location, school student gender and socio-economic status (full details in Randomisation section).

The second intervention stage will occur directly after the 12-month follow-up and involve individual-level randomisation. Stage I of the trial will have eight measurement occasions: baseline (pre-intervention); Stage I post intervention (immediately after completing the Stage I intervention, 6 weeks after baseline); and 6-month, 12-month (primary endpoint), 24-month, 36-month, 48-month and 60-month follow-up. The follow-up period is the time since baseline. For the subset of participants involved in Stage II of the trial, an additional measurement occasion will take place 6 weeks after the Stage II intervention (Stage II post intervention). The trial will take place in three recruitment waves. It was planned that Wave 1 will commence in Term 3, 2019 (July 2019), Wave 2 will commence in Term 2, 2020 (April 2020) and Wave 3 will commence in Term 3, 2020 (July 2020). The Stage I intervention phase (SPARX) will last 6 weeks and have a follow-up period of 5 years. The Stage II intervention phase (Sleep Ninja) will last 6 weeks, occurs 12 months after Stage I (SPARX) and will have a follow-up period of up to 4 years.

Data from each assessment point will be used to determine safety and whether any modifications to the trial protocol are required (see Analysis section for details). A concurrent implementation process evaluation will be conducted, and study processes may be modified to better address the needs of the school context. Any change will be reflected in the study protocol and registration (ACTRN12619000855123).

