### Outcomes

The administration schedule for each of the assessment measures described in the following is presented in Table 1.

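### The risk protocol promises SIDAS and YRBS at every assessment, but Table 1 omits both at 6 months and at Stage II post intervention

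*Protocol article*

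**What the plan says.** The Participant risk management protocol makes an unqualified commitment: "All students involved in the trial will be assessed for suicidal thinking and behaviour at each assessment point, using the SIDAS and the YRBS". The same section says that a survey response indicating serious suicidal thinking, plans or behaviour alerts the research team and the school counsellor, who follows up within 48 hours. Under Interim analyses, the DSMC is to review suicidality in both groups at every assessment, together with PHQ-A caseness and scores.

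The Outcomes section gives Table 1 its status: "The administration schedule for each of the assessment measures described in the following is presented in Table 1". In Table 1 the SIDAS and YRBS rows are ticked at baseline, Stage I post intervention, 12, 24, 36, 48 and 60 months. Both rows have a dash at 6 months and at Post (Stage II).

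The article treats those two occasions as assessments. The abstract says "Assessments will occur post intervention (both trial stages) and at 6, 12, 24, 36, 48 and 60 months post baseline". Trial design says "Stage I of the trial will have eight measurement occasions" and includes 6 months among them. For Stage II participants it adds that "an additional measurement occasion will take place 6 weeks after the Stage II intervention".

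**The concern.** The two statements describe different safety screening. A survey programmed from Table 1 would not carry the instruments that the risk section says every student completes.

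The only item-level suicide trigger that the article names is SIDAS item 3, described under Suicidal Ideation Attributes Scale, and SIDAS is absent at both occasions. The single self-harm item is also dashed at both. The PHQ-A is given at both, but the article names no PHQ-A item or threshold as a trigger for the risk procedure.

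What is at stake is safety monitoring in 12- to 14-year-olds. Stage II participants are selected for elevated depressive symptoms, and the affected survey is the one that follows their second intervention. A DSMC that relies on the text could also read data that were never collected as an absence of signal.

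**Working it through.** **Step 1: count the scheduled occasions.** The inputs are the nine column headers and three rows of Table 1. Each row has nine complete cells, so broken table layout does not explain the dashes.

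| Occasion | PHQ-A | SIDAS | YRBS |
|---|---|---|---|
| Baseline | yes | yes | yes |
| Post (Stage I) | yes | yes | yes |
| 6 months | yes | **no** | **no** |
| 12 months | yes | yes | yes |
| Post (Stage II), Stage II participants only | yes | **no** | **no** |
| 24 months | yes | yes | yes |
| 36 months | yes | yes | yes |
| 48 months | yes | yes | yes |
| 60 months | yes | yes | yes |
| Total | 9 of 9 | 7 of 9 | 7 of 9 |

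The table footnote restricts Post (Stage II) to Stage II participants. Without that row, every other student has eight occasions, and SIDAS and YRBS appear at 7 of 8. The risk section implies 9 of 9 and 8 of 8.

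**Step 2: length of the gaps.** Stage I post intervention is 6 weeks after baseline (Trial design). The next SIDAS and YRBS are at 12 months, so the interval for every student is 52 − 6 = 46 weeks. For Stage II participants there is a second interval, from 12 to 24 months, which contains the Stage II intervention and its post-intervention survey.

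**Step 3: what later surveys recover.** The three YRBS items ask about the past 12 months. The 12-month survey therefore reaches back over the 6-month point, and the 24-month survey over Stage II post intervention. Thoughts, plans and attempts can be recovered for a later comparison of arms, but not for an alert at the time. SIDAS covers the past month only, so its score at the two occasions is not recovered.

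**Step 4: how many students are surveyed without the instruments.**

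- *6 months.* The target is up to 10,000. The Sample size section allows 30% attrition by 12 months: 10,000 × 0.70 = 7,000. Taking no attrition and the full 12-month attrition as bounds gives 7,000 to 10,000.
- *Post (Stage II), as the plan states it.* Entrants: 7,000 × 0.20 × 0.75 × 0.50 = 525. With endpoint data: 525 × 0.70 = 367.5, about 368. Both match the Sample size section.
- *Post (Stage II), intervention arm only.* The plan's 7,000 covers both arms, whereas The current study confines Stage II to the intervention arm. At 1:1 allocation: 3,500 × 0.20 × 0.75 × 0.50 = 262.5, about 263 entrants, and 262.5 × 0.70 = 183.75, about 184 with endpoint data. Supplementing the Stage II sample, which the plan says it will consider, would raise these.

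**The case against.** The strongest reply is that the short batteries are deliberate and only the sentence is loose. At 6 months Table 1 schedules nothing but the PHQ-A, and the Hypotheses and Secondary outcome measures sections also leave 6 months out for the secondary outcomes. That is persuasive about intent at 6 months. It identifies which statement may need changing but does not reconcile the two.

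A second reply is that the commitment concerns all students, and Stage II post intervention is never given to all students, so it may fall outside the sentence. This reading is arguable, and it makes 6 months the clearer half of the conflict. However, the abstract and Trial design both list the Stage II occasion as an assessment.

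Third, screening may be adequate in practice. The alert wording covers study surveys in general, the PHQ-A is given at both occasions, and item-level rules may sit in the full protocol, which is not shown. Stage II entrants are also screened just before they start, since "The second intervention stage will occur directly after the 12-month follow-up". All of this stands, so no missed alert is claimed and the absence of a PHQ-A trigger rule is not counted as an omission. Nor does the article show whether the text or the table governs the survey build. If the text governs, the table is the part in error.

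Finally, Interim analyses names no instrument. By itself it does not contradict Table 1; it does so only when read with the risk section. It is supporting context here.

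**Conclusion.** The concern holds. The risk section and the administration schedule contradict each other, and nothing else in the article resolves it. The named instruments are scheduled at 7 of 9 occasions for Stage II participants and at 7 of 8 for everyone else, against a commitment to all of them.

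The practical consequence depends on Table 1 being what is built. In that case about 7,000 to 10,000 students are surveyed at 6 months without either instrument. At Stage II post intervention the number is roughly 184 to 263 (intervention arm only) or 368 to 525 (the plan's own figures). These ranges assume that the 10,000 target is met and use the plan's attrition and uptake rates. They are not counts of missed risk.

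This is a safety-monitoring inconsistency that should be fixed. It has no bearing on the primary endpoint, power or primary analysis.

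**What to change.** Decide which statement is intended and make the other agree.

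- **Preferred on safety grounds:** add SIDAS (five items) and the YRBS items (three) to Table 1 at 6 months and Post (Stage II), or at least the items that drive the alert. Coverage becomes 9 of 9 and 8 of 8. The cost is a protocol amendment, up to 5 + 3 = 8 more existing electronic items at each of two occasions, and more alerts for school counsellors to handle.
- **If the short batteries are intended:** limit the statement in the Participant risk management protocol to baseline, Stage I post intervention and 12, 24, 36, 48 and 60 months, and qualify Interim analyses to match. State what triggers an alert at 6 months and at Stage II post intervention, and tell the DSMC that those two occasions carry PHQ-A data but no SIDAS or YRBS data. The cost is one narrower sentence in each section plus a stated trigger rule.
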